#### 8.4. REPORTING AND RECORDING OF ADVERSE EVENTS

All symptoms or diseases observed by the physician or reported by the volunteer upon indirect questioning and which were not present at the initial examination (Visit 1) must be recorded as an adverse event.

Documentation regarding the adverse event should be made as to the nature, date of onset, end date, seriousness, severity, rate of appearance, corrective therapy, relation to trial medication, action(s) taken and outcome of any signs and symptoms. In any case, the volunteer has to be followed carefully until the adverse event has resolved or at least stabilized. If there is a worsening of a medical condition that was present before starting the trial, this should be considered as an adverse event and a complete evaluation should be recorded.

The trial medications relationship to each adverse event should be determined by the investigator based on the definitions detailed above.

All information regarding adverse events must be recorded in the specific AE pages of the CRF.

#### 8.5. REPORTING, RECORDING AND HANDLING OF SERIOUS ADVERSE EVENTS (SAES)

Any serious adverse event must be reported to benepharma within 24 hours.

All information regarding the experience must be recorded on a Serious Adverse Event (SAE) form. The patient should be followed carefully until the condition

disappears and/or the aetiology has been determined and all follow-up information has been obtained and recorded on the SAE form.

## **9 DATA MANAGEMENT AND STATISTICS**

### **9.1. DATA MANAGEMENT**

Data entry will be performed by the study site. The data will be entered by an authorized person onto a computer database.

All data entered onto the database will be checked again for accuracy and completeness using a trial specific computer-checking program. Any query resulting from this second check will be documented on a data correction form, answered by the investigator allowing correction of the database.

Programming of data checks, volunteer listings, summary tables and statistical tests will be performed by the Data Management and/or Statistician.

### **9.2. BLIND REVIEW**

The ICH-Biostatistics Guideline E9 [31] recommends a blind review before the decoding process . This will be done for two purposes:

- To define data sets/populations with discussion of each problem case in a blinded manner.
- To check and eventually to amend the analysis plan, based on newly gained information in this domain of research and also based on first blinded data analyses.

After signing and dating meeting minutes the study may be unblinded concerning the type of study drug. A written confirmation of the database lock has to be issued by the responsible statistician, before code break.

### **9.3. SAMPLE SIZE CALCULATION**

The sample size is difficult to calculate. In a previous thesis of our group sputum weight was found to be of little variation at two separate time points in patients with asthma. After inhalation of hypertonic saline induced sputum of 20 asthmatics was  $4.9 \pm 2.41$  g and  $4.78 \pm 1.6$  g respectively.

These data are in keeping with a previous publication in chronic bronchitis with bronchiectasis. The authors found after inhalation of hypertonic a sputum weight of 5.3 g compared to 3.17 g after saline inhalation (24).

Therefore the calculated sample size of the present study is based on an expected difference for Tacholiquin ® in sputum weight of about 1.2 g corresponding to about 40% of that expected for saline with a standard deviation of  $s=1.7$  g roughly

corresponding to a correlation between sputum weights of  $\rho=0.75$ . Then a sample size of 20 achieves a power of 80%.

#### **9.4. ANALYSIS OF EFFICACY CRITERIA**

The primary endpoint is sputum weight after 3 weeks of Tylaxopol– that after 3 weeks of saline treatment which will be analyzed for the Per Protocol Population. Estimated differences will be presented together with 95% confidence intervals (CIs) for the difference and two-sided p-values from a corresponding t-test. This analysis will be repeated for the ITT Population.

Secondary endpoints: The analysis of symptom scores ((CAT, BDI and TDI), ease of sputum production by analog scale, lung function parameter (FVC, FEV1, MEF25, RV, RV/TLC), will use the same methodology as that for the primary endpoint, using the ITT population. The analysis will include Day 1 and week 3 data. In addition acute changes of sputum weight on Day 1 at each treatment arm will be analyzed as described for the primary parameter. Secondary analyses aim to determine the efficacy BP versus placebo to modulate CRP and reducing the symptoms.

Data will be summarized with respect to demographic and baseline characteristics, efficacy observations and measurements, and safety observations and measurements.

Primary and secondary confirmatory analyses will be performed and reported at the end of the double-blind treatment period. A full statistical analysis plan will be produced prior to unblinding the study.

Biomarker profiles (sputum cells, IL-1, IL-6, IL-8), in sputum will be analyzed using an analysis of covariance (ANCOVA) model with covariates of baseline, smoking status and treatment. Estimated treatment differences along with corresponding 95 % CIs will be presented for the treatment comparison.

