## **5.3. DOSAGE AND TREATMENT SCHEDULE**

The dosage regimen will be three inhalations with 5 ml solution via nebulizer per day of study treatment during 21 consecutive days. Patients will be randomized either starting with Tacholiquin ® or Saline 0.9% in treatment phase A. After treatment phase A patients will receive the alternative drug in treatment phase B.

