**6.3. REPLACEMENT OF DROP-OUTS AND WITHDRAWALS**

It will be documented whether or not each patient completed the clinical study. If for any patient either study treatment were discontinued the reason will be recorded. Patients terminating the study prematurely will not be replaced. An estimation of 4 patients dropping out of the study has been considered when determining the number of patients to be recruited.

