#### **9.5. EXPLORATORY ANALYSIS OF EFFICACY CRITERIA**

All statistical tests will be two-sided using  $\alpha=0.05$ . An appropriate pooled center algorithm will be defined prior to unblinding the data. No adjustment for multiple testing will be done since the primary variable and the primary population is well defined.

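### The primary crossover t-test ignores period: a period effect would widen the interval and cost power, and would bias the estimate if the analysed sequences are unequal

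*Protocol*

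**What the plan says.** Protocol section 9.4 defines the endpoint and assigns it to the per-protocol set: "The primary endpoint is sputum weight after 3 weeks of Tylaxopol– that after 3 weeks of saline treatment which will be analyzed for the Per" (the quotation stops mid-phrase). The test is given next: "Estimated differences will be presented together with 95% confidence intervals (CIs) for the difference and two-sided p-values from a corresponding t-test". The synopsis and sections 2.2 and 7.1.1 name the same test. Section 9.4 sends the symptom scores, ease of expectoration, lung function and day 1 sputum weight to the same method. Section 9.5 adds "All statistical tests will be two-sided using" a 0.05 level.

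On the design, section 5.3 has patients randomised to start with either product, and "After treatment phase A patients will receive the alternative drug in treatment phase B". Section 5.5.1 allocates by permuted blocks of undisclosed size. Section 6.3 states "Patients terminating the study prematurely will not be replaced".

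No section names a period, sequence or carry-over term. The ANCOVA models for biomarkers (section 9.4) and for lung function (section 6.2.2) list none either. Section 9.4 promises a full SAP before unblinding; it is not at hand.

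**The concern.** A two-period crossover randomises patients to sequences so that a change between periods can be separated from the treatment effect. A t-test on the treatment difference, pooled over sequences, does not use that information. A shift between periods raises the difference in patients who take tyloxapol second and lowers it by the same amount in those who take it first. That spread is counted as random error. It cancels from the mean only when the two sequences contribute equal numbers.

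A shift is possible here. The two primary measurements, at visits 3 and 6, fall at about weeks 3 and 7, and sputum is collected at all six visits, so patients gain practice. Equal numbers are not assured either: drop-outs are not replaced, and section 9.4 names a per-protocol primary set. At stake are the precision and power of a trial planned to analyse 18 to 20 patients and, under imbalance, a bias that the randomised sequences could remove.

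**Working it through.** **Inputs.** Section 9.3 gives an effect "in sputum weight of about 1.2 g corresponding to about 40% of that expected for saline" and an SD of 1.7 g, described as "corresponding to a correlation between sputum weights of" 0.75. That SD is read as the SD of the within-patient difference: 1.7 = s × √(2 × (1 − 0.75)) gives s = 2.40 g per period, close to the 2.41 g that section 9.3 quotes for one of its time points. Alpha is 0.05 two-sided. The synopsis allocates 20 and analyses 18 per protocol; section 3 enrols 24, expects 4 drop-outs and aims for 20 evaluable. A 1:1 allocation is assumed, because no ratio is stated.

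**The plan's own figure.** One-sample t-test on differences, noncentral t:
- n = 18: SE = 1.7/√18 = 0.401; 1.2/0.401 = 2.99; df 17; power 80.6%.
- n = 20: SE = 1.7/√20 = 0.380; 1.2/0.380 = 3.16; df 19; power 84.9%.

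The smallest n for 80% is 18, so the stated 20 for 80% fits a paired t-test and is slightly conservative.

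**Model.** Let τ be the treatment effect, π the period effect (period 2 minus period 1), n1 the patients who take tyloxapol second, n2 those who take it first, and N = n1 + n2. The difference D has mean τ + π in the first group and τ − π in the second. Then:
- bias of mean D = π(n1 − n2)/N
- expected sample variance of D = 1.7² + π² × 4·n1·n2/(N(N − 1))

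At 10:10 the second term is π² × 20/19, so the expected SD is 1.704 at π = 0.12 g, 1.81 at 0.6 g, 1.91 at 0.85 g and 2.10 at 1.2 g.

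**Range for π.** The only time shift in the protocol is 4.9 − 4.78 = 0.12 g, in 20 asthmatics after hypertonic saline (section 9.3). The other values are assumptions: 0.6 g is half the target effect, 0.85 g is half the SD, and 1.2 g equals the target effect.

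**Power, plain t-test against period-adjusted** (plain test by simulation, at least 200,000 runs per cell):

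| π (g) | plain, 10:10 | plain, 9:9 |
|---|---|---|
| 0 | 85% | 81% |
| 0.12 | 85% | 80% |
| 0.6 | 82% | 77% |
| 0.85 | 78% | 73% |
| 1.2 | 71% | 65% |
| adjusted, any π | 84.7% | 80.3% |

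The adjusted estimate is half the difference between the two sequences' mean period differences. Its SE is (1.7/2) × √(1/n1 + 1/n2) on N − 2 df, and π drops out.

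**Bias, plain t-test.** Starting from 10:10 and losing two patients, the worst split is 10:8, where the bias is π × 2/18 = 0.11π: 0.01 g at π = 0.12, 0.07 g at 0.6 and 0.09 g at 0.85. At 11:7 it is π × 4/18 = 0.22π, or 0.13 g at 0.6. The sign depends on which sequence is larger. At 11:7 with π = 0.6 g, power is 85% if the bias favours tyloxapol and 67% if it opposes it.

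**Type I error, plain t-test.** At 10:10 it is 3.8% at π = 0.6 g and 1.7% at 1.2 g; at 12:8 it is 4.8% and 3.9%.

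**Cost of adjusting when π = 0.** At balance, 84.9 − 84.7 = 0.2 points (n = 20) and 80.6 − 80.3 = 0.3 points (n = 18). At 10:8 the adjusted test has 79.8% and at 11:7 about 78.3%, so the cost is roughly 1 and 2 points.

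**The case against.** The strongest reply is that the effect may be too small to matter. At the only time shift the protocol reports, 0.12 g, the plain t-test loses about 0.1 to 0.2 points of power, and even at 0.6 g it keeps 82% at n = 20. This stands as a limit on size. The figure does come from another disease and another inhalant, so it does not show that the shift is small here.

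The SAP is still to come, the blind review in section 9.2 may amend the analysis plan, and the wording of the test does not expressly say paired. All true. But the protocol itself names the test in four places, the endpoint is defined as treatment minus treatment, and the sample size reproduces as a paired test. An SAP that adds a period term would change the method the protocol names on its plain reading.

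Three stronger readings are tempting and do not hold:
- **False positives.** A reader might infer that the type I error rises. In the splits examined it stays at or below 5%, and well below at balance. What is inflated is the estimated variance.
- **Larger power loss.** Putting the inflated SD into the ordinary power formula gives 76% at 0.85 g and 68% at 1.2 g. At balance the period effect is a fixed shift that cancels from the mean, so only the estimated SE grows; the correct values are 78% and 71%. Similarly, 11:7 is a harsher split than the synopsis implies: going from 20 to 18 patients gives 10:8 at worst from equal sequences.
- **The ITT repeat.** Section 9.4 says "This analysis will be repeated for the ITT Population", and a reader might infer that this keeps only patients with both phases. The protocol does not say how patients with one phase are handled, and that may properly be set in the SAP.

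**Conclusion.** The point holds as a near-free improvement to a method that the protocol fixes. The planned t-test leaves period out, so a period effect makes the interval too wide and the test conservative and, with unequal sequences, shifts the estimate.

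The size depends on an assumed period effect. It is negligible at 0.12 g. At 0.6 g it costs about 3 points of power at 10:10 and 4 at 9:9; at 1.2 g, about 14 and 15. At the planned 18 per-protocol patients there is almost no power to spare, so 0.6 g already takes the plain test below 80%. Bias at 10:8 is modest: 0.09 g at 0.85 g, under a tenth of the 1.2 g target. These figures rest on 1.7 g being the SD of the difference, 1:1 allocation, normal data and no carry-over. The change should be made, but the trial does not fail without it.

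**What to change.** In section 9.4, and in the matching text of the synopsis and sections 2.2, 2.3, 7.1.1 and 7.1.2, replace the plain t-test with a period-adjusted crossover analysis, and apply it to every endpoint that inherits the primary method. Either form will do: a two-sample t-test comparing period differences between sequences, or a linear model with treatment, period and sequence fixed and patient random. With complete data the two agree. Report the treatment difference with its 95% CI.

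The cost is a wording change before unblinding and one degree of freedom: about 0.2 to 0.3 points of power at balance and about 1 to 2 points at 10:8 or 11:7. No new data are needed, and the smallest N for 80% power stays 18 (9:9). The period term does not remove carry-over.

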### **2.3. SECONDARY AND EXPLORATIVE ENDPOINTS**

Secondary endpoints:

The analysis of symptom scores ((CAT, BDI,TDI and St George's respiratory Quality of Life Questionnaire), ease of sputum production by analog scale, lung function parameter (FVC, FEV1, MEF25, RV, RV/TLC), LCI will use the same methodology as that for the primary endpoint, using the ITT population. The analysis will include Day 1 and week 3 data. In addition acute changes of sputum weight on Day 1 at each treatment arm will be analyzed as described for the primary parameter.

Explorative endpoints:

Biomarker profiles (sputum cells, IL-1, IL-6, IL-8), in sputum will be analysed using an analysis of covariance (ANCOVA) model with covariates of baseline, smoking status and treatment. Estimated treatment differences along with corresponding 95 % CIs will be presented for the treatment comparison.

In addition anti-inflammatory activity of tyloxapol will be analyzed in vitro by the macrophage activation test.

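### Protocol 9.4 calls the secondary analyses confirmatory, but 9.5 tests them all at unadjusted two-sided 0.05 for a reason that covers only the primary test

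*Protocol*

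**What the plan says.** Protocol section 9.4 gives primary and secondary analyses the same status: "Primary and secondary confirmatory analyses will be performed and reported at the end of the double-blind treatment period". Section 9.5, headed as exploratory analysis, fixes the level for everything: "All statistical tests will be two-sided using" α = 0.05. It then closes the question of multiplicity: "No adjustment for multiple testing will be done since the primary variable and the primary population is well defined".

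The secondary endpoints in 9.4 are the symptom measures ("CAT, BDI and TDI), ease of sputum production by analog scale") and "lung function parameter (FVC, FEV1, MEF25, RV, RV/TLC"), nine variables in all. Section 2.3 adds two more: the St George's questionnaire ("BDI,TDI and St George's respiratory Quality of Life Questionnaire") and the lung clearance index ("LCI will use the same methodology as that for the primary endpoint, using the ITT population"). Both sections say: "The analysis will include Day 1 and week 3 data". Both also add the acute change in sputum weight on Day 1, analysed like the primary endpoint.

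The protocol gives no order of testing, no condition that the primary must succeed first, and no split of alpha.

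**The concern.** A single, well-defined primary endpoint is a good reason not to adjust the primary test. It says nothing about the error rate across a set of other tests. That is harmless while the other tests are supportive. Once they are called confirmatory, the label suggests an error control that the plan does not provide.

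What is at stake is what the trial may conclude. The wording leaves room to report any one of many symptom or lung-function results with p < 0.05 as a confirmatory finding, even if sputum weight shows no difference. The protocol promises a full analysis plan before unblinding, but it does not leave this matter open for that plan. It assigns the confirmatory label and rules adjustment out, so the conflict lies in the present text.

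**Working it through.** **The plan's own figures.** The protocol states no error rate for the secondary analyses. Its only related figure is the primary sample size in 9.3: difference 1.2 g, SD 1.7 g, n = 20, power 80%. Taking 1.7 g as the SD of the within-patient difference, the noncentrality is 1.2/1.7 × √20 = 3.16. The paired t-test (19 df, two-sided 0.05) then has 84.9% power at n = 20, and 80.6% at the synopsis per-protocol number of 18. The primary test is adequately sized on these inputs and is not in question here.

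**Counting the secondary tests.** The text allows several readings.

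- *Every variable tested at Day 1 and at week 3.* From 9.4: 9 × 2 + 1 (Day 1 sputum weight) = 19. With the two additions in 2.3: 11 × 2 + 1 = 23.
- *Following the visit lists in 6.2.1.* BDI is taken only at Visits 1 and 4, and TDI only at Visits 3 and 6, so each has one time point per phase. From 9.4: 7 × 2 + 2 + 1 = 17. From 2.3: 9 × 2 + 2 + 1 = 21. The lung clearance index is listed only at Visits 1 and 6, which gives no like-for-like pair across treatments. Without it, the 2.3 count is 19.
- *Day 1 as the baseline for week 3, with BDI/TDI as one measure.* From 9.4: CAT, BDI/TDI, ease of expectoration and five lung-function variables make 8, plus Day 1 sputum weight = 9. With St George's: 10.

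The range is therefore about 9 to 23. CRP, named as a secondary aim in 9.4, is not counted and would add to it.

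**Chance of at least one false positive, independent tests, no drug effect.** In either direction this is 1 − 0.95^k. In favour of the drug only, it is 1 − 0.975^k.

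| k | Either direction | In favour of the drug |
|---|---|---|
| 9 | 37.0% | 20.4% |
| 10 | 40.1% | 22.4% |
| 17 | 58.2% | 35.0% |
| 19 | 62.3% | 38.2% |
| 21 | 65.9% | 41.2% |
| 23 | 69.3% | 44.1% |

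**Allowing for correlation.** The protocol gives no correlations between endpoints, so these are assumptions. I simulated paired t-tests with n = 20 and one common correlation between the within-patient differences, each oriented so that positive favours the drug (50,000 trials per cell).

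| Correlation | k = 9: either / in favour | k = 23: either / in favour |
|---|---|---|
| 0.3 | 33% / 17% | 59% / 31% |
| 0.5 | 28% / 14% | 46% / 23% |
| 0.7 | 21% / 10% | 32% / 16% |

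A single two-sided test at 0.05 carries 5% in either direction and 2.5% in the favourable direction. Across these readings and correlations the favourable-direction risk is about 4 times (10.4/2.5) to 18 times (44.1/2.5) that of one test.

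**The case against.** One primary endpoint with unadjusted secondary tests is a common design. The sentence in 9.4 is about when analyses are performed and reported. No passage says that a secondary result with p < 0.05 will be claimed as confirmed, still less that it will be claimed after a failed primary. The no-adjustment rule stands under an exploratory heading, which suggests that the authors may not have meant the secondary tests as confirmatory. All of this is fair, and it makes the matter a conflict of labels rather than proof of a planned overclaim. It does not remove the conflict, because 9.4 uses the word confirmatory for secondary analyses and nothing in the protocol withdraws it.

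Two stronger readings are tempting, and the documents do not support them.

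- A reader might infer that a false confirmed benefit is likely. The 62% to 69% that would suggest this needs the largest counts (19 to 23), independent tests, and false harm counted along with false benefit. FEV1, FVC, MEF25, RV and RV/TLC come from the same patients and test sessions, so independence is the least plausible case. In favour of the drug, the chance stays below 50% on every reading.
- A reader might infer that the reason in 9.5 also fails because the primary population is contradictory, since 9.7 assigns intent-to-treat to the primary and secondary analyses. But 9.7 also assigns per protocol to the primary efficacy analysis, and 2.2, 7.1.1 and 9.4 all name per protocol. The wording of 9.7 is awkward, but that is a separate matter from multiplicity.

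**Conclusion.** The point holds as a contradiction in the text: a confirmatory label on secondary analyses, no adjustment, order or gate, and a justification that reaches only the primary test. The error rate across the secondary tests is well above 5% on every reading of the count. How far above depends on two things the protocol does not settle: how many tests there are and how strongly the endpoints are correlated. The independence figures are an upper guide, and the figures at a correlation of 0.7 illustrate strong dependence. The type I error of the primary test is untouched, and nothing here bears on the sample size.

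**What to change.** In 9.4, replace the sentence with one to this effect: *The primary analysis is confirmatory; all secondary analyses are supportive and their p-values are descriptive.* Section 9.5 can then stand, because its reason matches its scope.

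If the sponsor wants a confirmatory secondary claim, name one or two week-3 endpoints and test them in a fixed order at two-sided 0.05, only after a significant primary result. That keeps the overall error rate at 0.05 without splitting alpha.

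The cost is one sentence, or a short paragraph for the second option. Sample size, data collection and the primary test do not change. The sponsor gives up confirmatory wording for the remaining secondary results.

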| OUTCOME(S)                           | The primary outcome variable is sputum weight after treatment as difference between that after Tylaxopol and after saline. Key secondary endpoint(s) are: symptom scores (CAT, BDI and TDI), ease of sputum production by analog scale, changes in lung function parameter (FVC, FEV1, MEF25, RV, RV/TLC), LCI, sputum parameters and biomarker profiles (IL-1, IL-6, IL-8), in sputum and response to Tylaxopol vs. saline. Assessment of safety: Safety will be ensured by monitoring of symptom scores and rescue medication, lung function FEV1 and adverse events. |
| DURATION OF TREATMENT AND FOLLOW-UP  | Duration of treatment per treatment arms (3 weeks): Each patient will be treated in a cross-over double-blinded randomized design either with Tylaxopol and or saline. During each treatment arm is a one week washout phase.                                                                                                                                                                                                                                                                                                                                                  |
| STUDY TYPE                           | This study is a monocenter double-blind, placebo-controlled (DBPC) crossover randomised trial.                                                                                                                                                                                                                                                                                                                                                                                                                                                                                        |

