### 6.2. **PROCEDURE BY VISIT**

#### 6.2.1. **METHODS AND MEASUREMENTS**

##### **Visit procedures at screening visit and before treatment phase A (Visit 1)**

- Patient information/Informed consent
- Date of visit
- Demographic data,
- Medical history and concomitant diseases
- Physical examination / Vital signs
- Concomitant medications
- Bodyplethysmography
- Bronchodilator response to Salbutamol
- Completing Questionnaires (CAT, BDI, St George)
- Inclusion/exclusion criteria

- Randomisation and drug dispensation
- Laboratory examination (including Urinalysis)
- Inhalation of blinded medication by nebuliser
- Sputum collection
- Recording side effects
- Recording “ease of expectoration”.
- Lung function monitoring up to one hour after sputum collection
- Lung clearance index one hour after inhalation
- Dairy explanation
- Appointment for the next visit

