### 7.3. **LABORATORY ASSESSMENTS**

#### 7.3.1. **SPUTUM PROCESSING**

Induced sputum will be analyzed for cell differentiation, as well as protein levels of cytokines.

Sputum will be sampled and processed as follows:

Subjects first inhale 200 µg Salbutamol and consecutively nebulised the study medication. During this procedure, it will be important to flush and clean the nose for disposal of lower part of squamous epithelium cells in the samples. Sputum will be processed within 2 hours of collection. The selected sputum plugs should be as far as possible without saliva, processed into a weighed Eppendorf tube and processed with 4x weight/volume of 0.1% Dithiothreitol. Afterwards 2x weight/volume of Phosphate-buffered saline (PBS) was added. Samples will be filtered through 48 µm mesh and centrifuged for 10 minutes at 790 x g to remove the cells. Supernatants will

be stored at -80C° until further analysis with Cytometric Bead Array (CBA) as described (26).

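### The explorative sputum-biomarker ANCOVA ignores the crossover pairing and period, and a per-period baseline would be a post-dose sample that can distort the treatment effect

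*Protocol*

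**What the plan says.** - **Design.** The study synopsis states: "This study is a monocenter double-blind, placebo-controlled (DBPC) crossover randomised trial". Under Section 5.3 each patient takes one treatment for 21 days in phase A and the other in phase B, so each patient supplies two end-of-treatment values.
- **Biomarker model.** Section 2.3 classes these endpoints as explorative: "Biomarker profiles (sputum cells, IL-1, IL-6, IL-8), in sputum will be analysed using an analysis of covariance (ANCOVA) model". Section 9.4 gives the terms: "analysis of covariance (ANCOVA) model with covariates of baseline, smoking status and treatment". The synopsis and Section 7.1.2 carry the same three-item list. None of these places names a patient, sequence or period term, and none defines baseline.
- **How sputum is obtained.** Under Section 7.3.1 patients inhale salbutamol "and consecutively nebulised the study medication", and the sputum is sampled from that procedure. The Visit 1 list in Section 6.2.1 puts "Inhalation of blinded medication by nebuliser" before sputum collection, and Visit 4 has the same order. No pre-dose sputum sample is described.
- **Day 1 sputum as an outcome.** Section 2.3 adds: "In addition acute changes of sputum weight on Day 1 at each treatment arm will be analyzed as described for the primary parameter".
- **Contrast with the primary endpoint.** Sections 2.2 and 9.4 analyse sputum weight as the tyloxapol-minus-saline difference with a t-test, which uses the pairing.

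**The concern.** There are two separate problems.

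First, the listed model suits a parallel-group trial. A patient's two outcomes are correlated, but with only baseline, smoking status and treatment in the model they are handled as independent rows. Smoking status is recorded once per patient and cannot stand in for a patient effect. Leaving out period also removes protection against a time trend if the two sequences end up unequal.

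Second, no drug-free sputum baseline exists. Any sputum baseline is taken after a dose of the blinded treatment. If the baseline is period-specific, it is a post-treatment variable that may already carry part of the effect being estimated.

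At stake is the trial's in vivo evidence on whether tyloxapol changes airway inflammation: its precision in every case, and its size and direction under one reading of baseline.

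**Working it through.** **Inputs.** From the protocol: 20 patients and a correlation of 0.75 between sputum weights (Section 9.3); "All statistical tests will be two-sided using" α = 0.05 (Section 9.5); permuted-block randomisation (Section 5.5.1), taken as 10 patients per sequence. The protocol gives no correlation or effect size for biomarkers. Assumed here: correlation 0.75 with lower and higher values as a check, a true week-3 effect of 0.5 SD, and first-dose effects from −0.25 to 0.5 SD.

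**The plan's own figure.** The protocol gives a sample size only for sputum weight. Its SD of 1.7 g fits a within-patient difference: 2.41 × √(2 × (1 − 0.75)) = 1.70. A paired t-test for 1.2 g then needs 18 patients for 80% power (80.6%), and 20 give 84.9%. The figure reproduces within two patients as a paired calculation. Nothing comparable is stated for the ANCOVA.

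**Standard errors, in SD units.**
- Within patient: √(2 × (1 − 0.75)/20) = √0.025 = 0.158.
- ANCOVA as listed: √(2 × (1 − 0.75²)/20) = √0.04375 = 0.209.
- Ratio: 0.209/0.158 = 1.32.

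**Simulation** (4,000 trials per row, correlation 0.75, true effect 0.5 SD):

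| Model | First-dose effect | Estimate | Model SE | True SE | Coverage | 95% half-width | Power |
|---|---|---|---|---|---|---|---|
| ANCOVA, Visit 1 baseline for both periods | 0 | 0.50 | 0.204 | 0.159 | 0.986 | 0.42 | 68% |
| Same | 0.25 | 0.50 | 0.207 | 0.158 | 0.988 | 0.42 | 69% |
| ANCOVA, per-period baseline | 0 | 0.50 | 0.207 | 0.198 | 0.964 | 0.42 | 66% |
| Same | 0.25 | 0.31 | 0.210 | 0.198 | 0.886 | 0.43 | 29% |
| Same | 0.5 | 0.13 | 0.215 | 0.210 | 0.629 | 0.44 | 9% |
| Same | −0.25 | 0.68 | 0.210 | 0.196 | 0.884 | 0.43 | 90% |
| Patient + period + treatment | any of these | 0.50 | 0.156 | 0.155–0.159 | 0.95 | 0.33 | 83–85% |

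Half-width ratio: 0.42/0.33 ≈ 1.3. With no true effect and no first-dose effect, the ANCOVA's type I error is 0.012 (Visit 1 baseline) or 0.036 (per-period baseline).

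**Why the two readings differ.** A Visit 1 value used for both periods is identical in a patient's two rows. It cannot shift the treatment contrast, but the residual still contains between-patient variation, so the SE is too large. A per-period baseline differs between treatments by the first-dose effect *a*, and adjustment subtracts about 0.75 × *a*:
- *a* = 0.25: 0.50 − 0.1875 = 0.31, about 37% removed.
- *a* = 0.5: 0.50 − 0.375 = 0.125 (simulated 0.13), about 74% removed in simulation.
- *a* = −0.25: 0.50 + 0.1875 = 0.69 (simulated 0.68), inflated.
- *a* = 0.5 with no week-3 effect: simulated −0.365, significant in 36% of trials.

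**Other correlations.**
- At 0.5 with the Visit 1 baseline, power is 41–42% against 55–57%, half-width 0.55 against 0.47, and type I error 0.018.
- With per-period baselines and *a* = 0.25, 28–42% of the effect is removed for within-period correlations of 0.6 to 0.85.
- If a per-period baseline tracks its own period's outcome better than the other period's (0.85 against 0.7), the precision loss disappears (half-width 0.34 against 0.36), but the estimate is 0.29 and coverage 0.78.

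**Period.** With balanced sequences, omitting period causes no bias. With 11 and 7 completers and an assumed 0.5 SD period effect, the shift is 0.5 × (7 − 11)/18 = −0.11, giving 0.39 instead of 0.50. Section 6.3 expects four drop-outs without replacement, so some imbalance is plausible.

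**The case against.** The strongest reply is that these endpoints are explorative and unpowered, that Section 9.4 promises a full SAP before unblinding, and that the blind review in Section 9.2 may amend the analysis plan. Defining baseline and adding patient and period terms could be left to that stage. This limits the weight of the point but does not remove it: the protocol states a model, with treatment among its terms, in four places, and an SAP that follows it inherits the problem.

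A reader might also infer more than the documents support:
- **That the model will remove part of the effect whenever the drug acts on Day 1.** This needs a per-period baseline, which the protocol does not specify, and a same-direction first-dose effect on the biomarkers. Section 1.1.1 concerns sputum viscosity and volume; Section 1.1.3 describes cultured monocytes. Neither gives an acute airway biomarker effect. A first-dose effect as large as the three-week effect is an extreme case.
- **That the intervals are falsely narrow.** Without a first-dose effect the error is conservative. The clearest miscalibration (coverage about 0.99) arises under the Visit 1 reading, where there is no bias; under the per-period reading the SE is nearly right.
- **That the Day 1 sputum-weight analysis is invalid for want of a pre-dose weight.** It follows the primary method, a difference between treatments, so it is already a paired comparison of post-dose weights. Only the reference to change is loose.
- **That smoking status must be dropped.** No harm from keeping it has been shown.

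**Conclusion.** The point holds in a limited form. The biomarker model as stated ignores the pairing and omits period, and a free alternative does better. At a common correlation of 0.75 the cost is an interval about 1.3 times as wide and power of about 66–70% against about 85% for a 0.5 SD effect; at 0.5 it is about 42% against 57%. Distortion of the estimate is conditional: none with a Visit 1 baseline or without a first-dose effect, attenuation with a per-period baseline and a same-direction first-dose effect, and inflation with an opposite one. The biomarker correlations and all effect sizes are assumptions, and the 1.3 ratio shrinks or vanishes if a per-period baseline is much closer to its own period's outcome. The primary sputum-weight comparison is a within-patient difference and is unaffected. The change is worth making, but no confirmatory conclusion depends on it.

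**What to change.** In the synopsis, Sections 2.3, 7.1.2 and 9.4, and the SAP, replace the biomarker model with a within-patient analysis of the week-3 sputum values (Visits 3 and 6), with treatment and period as fixed terms and patient as a random or fixed term. State that the sputum values from Visits 1 and 4 are not used as per-period covariates because they are taken after study drug. If a Visit 1 value is kept for description, define it as a post-dose sample. Smoking status may stay or go. As an editorial matter, describe the Day 1 sputum-weight analysis as a comparison of post-dose weights at Visits 1 and 4.

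The cost is wording only, before unblinding; the blind review in Section 9.2 is a suitable occasion. No new samples, visits or patients are needed.
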